|                                                                                                                                                                                                                                                                                                                                                                                                                                                                                                                                                                                                                                                              | 171 |
| 4. Rate of cesarean sections and operative deliveries.                                                                                                                                                                                                                                                                                                                                                                                                                                                                                                                                                                                                       | 172 |
| 5. Neonatal outcomes: admission to the neonatal intensive care unit, Apgar score at 1 and 5 minutes from birth, neonatal hyperbilirubinemia and cord blood pH levels when taken.                                                                                                                                                                                                                                                                                                                                                                                                                                                                             | 173 |
|                                                                                                                                                                                                                                                                                                                                                                                                                                                                                                                                                                                                                                                              | 174 |
|                                                                                                                                                                                                                                                                                                                                                                                                                                                                                                                                                                                                                                                              | 175 |
| 6. Neonatal anthropometric measurements (birth weight and head circumference), fetal malformations and developmental disorders near birth.                                                                                                                                                                                                                                                                                                                                                                                                                                                                                                                   | 176 |
|                                                                                                                                                                                                                                                                                                                                                                                                                                                                                                                                                                                                                                                              | 177 |

|                                                                                                                                                                                                                                            |                                 |
|--------------------------------------------------------------------------------------------------------------------------------------------------------------------------------------------------------------------------------------------|---------------------------------|
| 7. Mean and lowest neonatal blood glucose values in preterm neonates.                                                                                                                                                                      | 178                             |
| 8. Maternal adverse effects (e.g gastrointestinal discomfort and allergic reaction).                                                                                                                                                       | 179                             |
| Study Drugs:                                                                                                                                                                                                                 | 180                             |
| • Name: metformin (metformin Teva, glucophage, glucomin)                                                                                                                                                                            | 181                             |
| • Manufacturer: Teva Pharmaceutical Industries Ltd (metformin Teva, glucophage), Dexcel Ltd, Israel (glucomin). If additional metformin tablets from additional manufacturers become available, they will be accepted as well.      | 182
183
184
185
186 |
| • The Side effects may include - Taste disturbance, nausea, vomiting, diarrhea, abdominal pain, hypoglycemia, bloating/abdominal distention, constipation and lactic acidosis ( very rare).                                         | 187
188
189               |
| • Storage at room temperature                                                                                                                                                                                                       | 190                             |
| • Maximal acceptable dose during pregnancy: 3,000 mg/day (21)                                                                                                                                                                              | 191                             |
| This medication was used in a previous study to treat maternal hyperglycemia during pregnancy with high efficacy and safety profiles (17). It was also used in non-diabetic pregnant women without severe significant adverse events (18). | 192
193
194               |
| Study randomization                                                                                                                                                                                                          | 195                             |
| Randomization will be done by computerized software according to power calculation inside sealed envelopes (concealment of allocation). In this way the study will be unbiased.                                                            | 196
197
198
199        |
| Statistics                                                                                                                                                                                                                   | 200                             |
| Categorical variables will be compared using Chi-square test or Fisher's exact test.                                                                                                                                                       | 201                             |
| Continuous variables will be compared via the Student's t-test or Mann–Whitney-U test.                                                                                                                                                     | 202
203                      |
| Sample size:                                                                                                                                                                                                                 | 204                             |
| We set two primary outcomes. Adjustment for multiplicity of the primary outcomes was made using the method described by Holm (22).                                                                                                         | 205
206                      |
| For the maternal outcome (mean maternal daily glucose value):                                                                                                                                                                              | 207                             |
| In order to demonstrate a mean difference of 5 mg% with 10 mg% standard deviation in the mean daily glucose charts 156 women will be required (two tailed                                                                                  | 208
209                      |

alpha=0.025,power of 80%). This assumption was chosen due to its clinical relevancy.

For the neonatal outcome from preterm deliveries (the rate of neonatal hypoglycemia in preterm deliveries):

In the study of Gyamfi-Bannerman et al (4), neonatal hypoglycemia following antenatal betamethasone and placebo were 24% versus 15%, respectively. In the same study around 16% of neonates were born at term and all neonates were older than 34 gestational age. We hypothesized that the rate of hypoglycemia will be higher in preterm neonates due to stronger effect of betamethasone administration but treatment with metformin will reduce the risk to the baseline. In order to show a reduction in preterm neonatal hypoglycemic from 40% in the control group to 15% in the metformin group, a sample size of 98 neonates will be required. In twins' pregnancy, each twin will be analyzed separately.

Recruitment will be done until completion of the sample size for both primary outcomes.

Since one third of the women are expected to deliver prematurely the estimated sample size+10% drop outs is: 323 women.

Number of participants form this center: 200

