 some of the studies (18). In the study of Nascimento et al (N=375 women), metformin 75  
 reduced the rate of cesarean delivery in non-diabetic obese pregnant women 76  
 compared to control. The rate of drug intolerance was reported to be only 4% (19). In 77

|                                                                                      |     |
|--------------------------------------------------------------------------------------|-----|
| the study of Dodd (N=524), the rate of adverse effect was similar between the        | 78  |
| metformin and control groups (20).                                                   | 79  |
| We hypothesize that metformin will reduce the rate of neonatal hypoglycemia of       | 80  |
| preterm neonates that their mothers were treated with betamethasone via reduction of | 81  |
| maternal hyperglycemia.                                                              | 82  |
| In the present study we will examine the effect of treatment with metformin on       | 83  |
| maternal glycemic control and hypoglycemia in preterm neonates following maternal    | 84  |
| betamethasone treatment.                                                             | 85  |
| Study aims                                                             | 86  |
| 1. To study the effect of metformin treatment on glycemic control in pregnant        | 87  |
| women who received betamethasone                                                     | 88  |
| 2. To study the effect of metformin treatment on neonatal hypoglycemia in            | 89  |
| preterm neonates born to pregnant women who received betamethasone                   | 90  |
| Study hypothesis                                                       | 91  |
| Metformin will improve glycemic control of pregnant women receiving                  | 92  |
| betamethasone and will reduce the rate of neonatal hypoglycemia of preterm infants   | 93  |
|                                                                                      | 94  |
| Study design                                                           | 95  |
| Multicenter, open-label, randomized, controlled study.                               | 96  |
| Number of medical centers: 5                                           | 97  |
| Study population                                                       | 98  |

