| 2. Control group will not receive treatment with metformin.                                                                                                                                                                                                                                                                                                                                                                                                                                                                                                                                                                                                      | 130
131                                           |
| Follow-up protocol                                                                                                                                                                                                                                                                                                                                                                                                                                                                                                                                                                                                                                        | 132                                                  |
| Pregnant women that are at increased risk for preterm delivery will receive intramuscular (IM) injection of 12 mg betamethasone (celestone) according to physician's discretion. If delivery does not occur, additional IM 12 mg betamethasone injection will be administered 24 hours following the first injection as accepted (women that will not receive the second injection will not be removed from the study and metformin will be administrated). Before or within 24 hours from the first betamethasone injection the women will be enrolled to the study and will be allocated randomly to either the research or control groups as described above. | 133
134
135
136
137
138
139
140 |

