| In both groups blood glucose will be obtained according to the following schedule: before meals (pre-prandial), 90-120 minutes after starting meals (post-prandial) and at 10 p.m. The glucose chart will be filled from enrollment and up to 3-4 days following                                                                                                                                                                                                                                                                                                                                                                                                 | 141
142
143                                    |

|                                                                                                                                                                                                                                                                                                                                                                                                                                                                                                                                                                                                                                                              |     |
|--------------------------------------------------------------------------------------------------------------------------------------------------------------------------------------------------------------------------------------------------------------------------------------------------------------------------------------------------------------------------------------------------------------------------------------------------------------------------------------------------------------------------------------------------------------------------------------------------------------------------------------------------------------|-----|

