| Demographic, background and obstetrics characteristics will be collected. Adverse effects with possible relation to metformin will be documented. In addition, for neonates born prematurely, data regarding neonatal metabolic complications that are routinely assessed will be collected from the neonatal medical charts. Those include: umbilical cord pH, APGAR scores, hypoglycemia (defined as glucose levels < 40 mg/dL and 50 mg/dL during the first day and later on, if data from the first day is not available, respectively), hyperbilirubinemia (diagnosis is depended on gestational age as accepted), birth weight and head circumference. | 150 |
|                                                                                                                                                                                                                                                                                                                                                                                                                                                                                                                                                                                                                                                              | 151 |
|                                                                                                                                                                                                                                                                                                                                                                                                                                                                                                                                                                                                                                                              | 152 |

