| 2. Mean maternal daily post-prandial glucose values.                                                                                                                                                                                                                                                                                                                                                                                                                                                                                                                                                                                                         | 168 |
| 3. Percent of abnormal values in the daily glucose chart: pre-prandial values $\geq 95$ mg/dl, 90 minutes post-prandial values $\geq 130$ mg/dl, 120 minutes post-prandial values $\geq 120$ mg/dl and mean daily glucose > 95-100 mg/dl.                                                                                                                                                                                                                                                                                                                                                                                                                    | 169 |
|                                                                                                                                                                                                                                                                                                                                                                                                                                                                                                                                                                                                                                                              | 170 |

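### Maternal adverse effects are collected subject to a possible relation to metformin, in an open-label trial with untreated controls, and maternal hypoglycaemia is not defined as an outcome

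*Protocol*

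**What the plan says.** On adverse effects, the Follow-up protocol gives one collection rule: "Adverse effects with possible relation to metformin will be documented". It names no arm, no assessor and no method of judging relation. Under Study outcomes, secondary outcome 8 reads "Maternal adverse effects (e.g gastrointestinal discomfort and allergic reaction", an open list with no condition on relation to the drug.

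Study design describes a "Multicenter, open-label, randomized, controlled study", and the Intervention section states "Control group will not receive treatment with metformin". No placebo is described.

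On maternal glucose, the Follow-up protocol states "In both groups blood glucose will be obtained according to the following schedule", with readings before and after meals and at 10 p.m. The outcomes built on that chart are daily means (primary outcome 1, secondary outcomes 1 and 2) and the share of abnormal readings (secondary outcome 3: "Percent of abnormal values in the daily glucose chart: pre-prandial values"), where every limit is an upper one. The side-effect list under Study Drugs includes "Taste disturbance, nausea, vomiting, diarrhea, abdominal pain, hypoglycemia". A numerical definition of hypoglycaemia is given only for the neonate.

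**The concern.** A comparison of adverse effects between arms is fair only if the same events have the same chance of being recorded in each arm. A filter on relation to the study drug puts that at risk when one arm receives no study drug. A recorder who takes the rule causally has reason to leave out a control woman's nausea or abdominal pain and to record the same symptom under metformin. There is no blinding to protect against this, and five centres may each read the sentence differently.

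At stake is whether outcome 8 can separate symptoms caused by metformin from those these women would have had anyway. A later analysis plan cannot repair this, because a symptom never written down for a control woman cannot be recovered.

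The second part concerns what is reported. A low maternal reading lowers the daily mean and so counts towards apparent benefit on primary outcome 1. No outcome explicitly counts such readings as a possible harm.

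**Working it through.** The protocol states no adverse-effect rate and no figure on this point, so there is nothing of its own to reproduce. The check is a comparison of the texts, followed by an illustration.

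**Step 1: collection rule against outcome.**

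| Item | Collection rule (Follow-up protocol) | Secondary outcome 8 |
|---|---|---|
| Events covered | Those possibly related to metformin | Maternal adverse effects, open list |
| Relation filter | Yes | None |
| Arms | Not stated | Not stated |
| Who judges relation, and how for controls | Not stated | Not applicable |

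The rule is narrower in wording than the outcome. The glucose schedule, by contrast, is expressly set for both groups.

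**Step 2: maternal glucose outcomes against the side-effect list.** Secondary outcome 3 uses pre-prandial values of at least 95 mg/dl, 90-minute values of at least 130 mg/dl, 120-minute values of at least 120 mg/dl, and a daily mean above 95-100 mg/dl. None is a lower limit. Hypoglycaemia is on the protocol's own side-effect list, and the readings needed to count it are collected in both arms, but no outcome names or defines it.

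**Step 3: how much unequal recording could matter.** The inputs are:
- Women per arm: 323 / 2 = 161.5, taken as 161. The 323 comes from Sample size; 1:1 allocation is assumed, and the 10% drop-out allowance is not removed.
- True adverse-effect rate p, the same in both arms: 5%, 10% or 20% (assumed).
- Share r of control events recorded relative to the metformin arm: one half or one quarter (assumed).
- Two-sided level 0.05.

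The recorded rates are p under metformin and q = p × r in controls. With m = (p + q)/2 and n = 161:

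- SE0 = √[2m(1 − m)/n]
- SE1 = √[(p(1 − p) + q(1 − q))/n]
- chance of a false difference = Φ[(p − q − 1.96 × SE0)/SE1]

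For p = 10% and r = 1/2: q = 5% and m = 7.5%. SE0 = 0.3725/12.689 = 0.02936 and SE1 = 0.3708/12.689 = 0.02922. Then (0.05 − 1.96 × 0.02936)/0.02922 = −0.258, and Φ(−0.258) = 0.398.

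| True rate, both arms | Control events recorded half as often | Control events recorded a quarter as often |
|---|---|---|
| 5% | 5% v 2.5%: 22% | 5% v 1.25%: 49% |
| 10% | 10% v 5%: 40% | 10% v 2.5%: 80% |
| 20% | 20% v 10%: 71% | 20% v 5%: 98% |

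The last figure in each cell is the chance that the trial declares a difference that does not exist. With equal recording (r = 1) it stays at the nominal 5%.

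**The case against.** The strongest reply is that the sentence does not say what a strict reader takes from it. It does not contain the word only, and it is not confined to the metformin arm. It can mean the types of event that metformin may cause, such as those listed under Study Drugs, recorded in every woman. On that reading a control woman's vomiting is recorded, and the unfiltered wording of outcome 8 supports it.

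This stands. A reader might infer that the comparison is one-sided by construction, with some percentage under metformin against zero in controls. The documents do not support that: a zero in controls follows only if the strict reading is assumed, and that reading is the point in doubt.

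A reader might also infer that maternal hypoglycaemia would go unreported. That too goes beyond the text. As a listed side effect it falls within the collection rule and could be reported under the open list of outcome 8, and the charted readings remain available. The Introduction also cites trials in non-diabetic obese pregnant women (N=1099) in which metformin did not cause maternal hypoglycaemia. Nor should the women here be called normoglycaemic during treatment: the Introduction expects steroid-induced hyperglycaemia. A threshold might, moreover, be set in an analysis plan that is not at hand.

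What the reply does not remove is the ambiguity itself. The rule permits two readings, one of which spoils the comparison, and nothing in the protocol chooses between them. That is settled when data are collected, not in the analysis. The cited reassurance on hypoglycaemia comes from obese women, whereas the inclusion criteria here do not require obesity.

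**Conclusion.** The concern holds in a limited form. The stated rule is conditioned on relation to metformin, does not say how this applies to women who take none, and is narrower than secondary outcome 8. In an open-label trial this leaves the arm comparison open to one-sided ascertainment.

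The protocol gives no basis for estimating the bias. The illustrative range of 22% to 71% false differences rests on half-recording in controls, equal true rates of 5% to 20%, 1:1 allocation and about 161 women per arm. If both arms are recorded alike, there is no bias.

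Maternal hypoglycaemia is not excluded from reporting; it lacks an explicit name and definition as an outcome. Both points affect secondary safety reporting. Neither changes a primary outcome or the sample size. The change is worth making because it is cheap and the missing data could not be recovered later.

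**What to change.** Replace the adverse-effect sentence in the Follow-up protocol with a rule that all maternal adverse events are recorded in both arms, over the same window and with the same symptom list, irrespective of attribution. Collect the judgement of relatedness as a separate field, so that it describes events without deciding which are recorded. Outcome 8 can then be analysed as worded.

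Add to the safety outcomes, by arm, the number and share of women with any charted glucose below a reporting threshold that the sponsor fixes before data review. This is a reporting definition only and does not alter treatment.

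The cost is a change to the case report form and slightly more event recording in the control arm. The low-glucose count uses readings already collected.
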